## Abstract

**Background:**

Neonatal hypothermia is an important challenge associated with morbidity and mortality. Preventing neonatal hypothermia is important in high-resource countries, but is of fundamental importance in low-resource settings where supportive care is limited.

Kangaroo mother care (KMC) is a low-cost intervention that, whenever possible, is strongly recommended for temperature maintenance. During KMC, the World Health Organization (WHO) guidelines recommend the use of a cap/hat, but its effect on temperature control during KMC remains to be established.

In the hospitals participating in the projects of the non-governmental organization CUAMM, KMC represents a standard of care, but the heads of the babies often remain uncovered due to local habits or to the unavailability of a cap. The aim of the present study will be to assess the effectiveness and safety of using a woolen cap in maintaining normothermia in low-birth-weight infants (LBWI) during KMC.

**Methods/design:**

This is a multicenter (three hospitals), multicountry (three countries), prospective, unblinded, randomized controlled trial of KMC treatment with and without a woolen cap in LBWI. After obtaining parental consent, all infants with a birth weight below 2500 g and who are candidates for KMC, based on the clinical decision of the attending physician, will be assigned to the KMC with a woolen cap group or to the KMC without a woolen cap group in a 1:1 ratio according to a computer-generated, randomized sequence. The duration of the study will be until the patient’s discharge, with a maximum treatment duration of 7 days.

The primary outcome measure will be whether the infants’ temperatures remain within the normal range (36.5–37.5 °C) in the course of KMC during the intervention. In all participants, axillary temperature will be measured with a digital thermometer four times per day. In addition, maternal and room temperature will be recorded.

Secondary outcome measures will be: episodes of apnea; sepsis; mortality before hospital discharge; in-hospital growth; and age at discharge.

**Discussion:**

The findings of this study will be important for other units/settings in high- as well low-resource countries where KMC is routinely performed. Based on the results of the present study, we could speculate whether the use of a woolen cap may help to maintain the neonate within the normal thermal range. Furthermore, potential complications such as hyperthermia will be strictly monitored and collected.

**Trial registration:**

ClinicalTrials.gov Identifier: NCT02645526 (registered on 31 December 2015).

## Background

The days and weeks following childbirth – the postnatal period – is a critical phase in the lives of mothers and newborn babies. Most maternal and infant deaths occur during this time [1]. In this period, neonatal hypothermia is an important challenge associated with morbidity and mortality [2]. Hypothermia increases the newborn’s metabolic requirements and is associated with hypoglycemia, hypoxia, and ultimately severe infections and newborn mortality [3]. Preventing neonatal hypothermia is important in high-resource countries, but is of fundamental importance in low-resource settings where supportive care is limited.

Kangaroo mother care (KMC) is a low-cost intervention that has the potential to prevent many complications associated with preterm birth and may also provide benefits to full-term newborns [4].

KMC is care of a small baby who is continuously carried in skin-to-skin contact by the mother and exclusively breastfed (ideally). It is considered the best way to keep a small baby warm and it also helps to establish breastfeeding. KMC can be started in the hospital as soon as the baby’s condition permits (i.e., the baby does not require special treatment, such as oxygen or intravenously administered fluids) [5].

Whenever possible, KMC is strongly recommended for temperature maintenance [4]. During KMC, the World Health Organization (WHO) guidelines recommend the following approach: “clothe the baby with a pre-warmed shirt open at the front, a napkin, a hat, and socks” [5].

Previous studies show that neonatal heat loss following delivery may be reduced or prevented by the application of simple woolen hats [6–8], but the effect of a cap on thermal control of neonates during the first postnatal days remains to be defined. On the other hand, hyperthermia should also be avoided [9, 10].

Doctors with Africa CUAMM is a non-governmental organization supporting health programs in different African countries. In the hospitals participating in the CUAMM projects, KMC represents a standard of care, but the heads of the babies often remain uncovered due to local habits or, more simply, to the unavailability of a cap. However, although WHO guidelines recommend the use of a cap/hat during KMC, the effect on neonatal temperature during the days and weeks following childbirth has not been previously studied. It is unknown whether covering the head of the neonate with a woolen cap during KMC may help temperature maintenance. The results of the present study will allow us to understand whether the use of a cap during KMC is effective and safe.

Previous studies suggest that neonatal heat loss following delivery may be reduced or prevented by the application of a woolen hat [6–8]. These studies assessed patients immediately after birth and for a short period. On the other hand, hyperthermia can be dangerous to the newborn infant and should also be avoided [9, 10].

To our knowledge, there are no previously published studies that have evaluated the effect of using a woolen cap in the course of KMC.

The aim of the present study will be to assess the effectiveness and safety of using a woolen cap in maintaining normothermia in low-birth-weight infants (LBWI) during KMC.

## Methods/design

### Study design

This is a multicenter, prospective, unblinded, randomized clinical trial of KMC treatment with and without a woolen cap in LBWI.

### Setting

The study will be conducted at three hospitals that have three different levels of healthcare in three African countries where Doctors with Africa CUAMM has ongoing projects on maternal-neonatal health. They are:Central Hospital of Beira in Mozambique (5555 deliveries – CUAMM data 2013), which is a governmental hospital (III level) (Mozambique: neonatal deaths, 34 % of all under-5 deaths; neonatal mortality rate: 30 per 1000 live births; source: *Countdown to 2015, The 2014 Report*) (http://www.mediciconlafrica.org content/uploads/sites/2/2015/09/Health_and_Devel_71_giu15-BASSA.pdf)St. Luke Wolisso Hospital in Ethiopia (3323 deliveries – CUAMM data 2013), which is a no-profit zonal hospital (II level) (Ethiopia: neonatal deaths, 43 % of all under-5 deaths; neonatal mortality rate: 29 per 1000 live births; source: *Countdown to 2015, The 2014 Report*) (http://www.mediciconlafrica.org content/uploads/sites/2/2015/09/Health_and_Devel_71_giu15-BASSA.pdf)Aber Hospital in Uganda (1872 deliveries – CUAMM data 2013), which is a no-profit rural hospital (I level) (Uganda: neonatal deaths, 33 % of all under-5 deaths; neonatal mortality rate 23 per 1000 live births; source: *Countdown to 2015, The 2014 Report*) (http://www.mediciconlafrica.org content/uploads/sites/2/2015/09/Health_and_Devel_71_giu15-BASSA.pdf)

### Inclusion criteria

Infants satisfying the following inclusion criteria will be eligible to participate in the study:Birth weight below 2500 g (and)Candidate to KMC treatment (and)Parental consent: a written informed consent will be obtained by a member of the neonatal team involved in the study from a parent or guardian before KMC treatment

### Exclusion criteria

Major congenital malformationsTwinsParental refusal to participate in the study

### Procedure

After obtaining parental consent, all infants with a birth weight below 2500 g and who are candidates for KMC, based on the clinical decision of the attending physician, will be assigned to the KMC with a woolen cap group (KMC + cap) or to the KMC without a woolen cap group (KMC group). All the caps used for the study are handmade by a group of volunteers in Padova. The material (wool) was provided by CUAMM and sizes were standardized.

The procedure of initiating, maintaining and stopping the KMC will be based on WHO guidelines [5]. Mothers will be trained in monitoring the baby’s condition and in recognizing dangerous clinical signs during KMC [5]. The duration of the study will be until the patient’s discharge, with a maximum treatment duration of 7 days. In case of documented neonatal hypothermia (temperature below 36.5 °C) or hyperthermia (temperature above 37.5 °C) during the course of the study, the pre-warmed blanket will be added or removed. In case of maternal hyperthermia, we will ask the woman to wear lighter clothes. In these cases, neonatal and maternal temperatures will be measured every hour until the normal range is reached.

### Primary outcome measure

The primary outcome measure will be whether the infants’ temperatures remain within the normal range (36.5–37.5 °C) in the course of KMC during the intervention. In all participants, axillary temperature will be measured with a digital thermometer (C202; Terumo, Tokyo, Japan) every 6 hours during KMC treatment. Maternal and room temperature will be registered at the same time. Room temperature will be measured at the same times (every 6 hours) by using the same wall thermometers (Oregon Scientific RMR262) in all three study sites.

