### Statistical analysis

Analysis will be performed as per intention-to-treat. Continuous data will be expressed as mean and standard deviation (SD) or median and interquartile range (IQR). The effect of the treatment on primary outcome will be assessed using a Poisson model adjusting for hospital and a set of clinically relevant confounders (maternal temperature, environmental temperature, birth weight, postnatal age). The logarithm of the number of measurements during hospital stay will be used as an offset, in order to take into account the different lengths of hospital stay of each participant. The effect of the treatment on the number of episodes of apnea will be assessed using a Poisson model adjusting for hospital and a set of clinically relevant confounders (neonatal and maternal temperatures, environmental temperature, birth weight, postnatal age). The logarithm of the number of measurements during hospital stay will be used as an offset. The effect of the treatment on binary secondary outcome (sepsis and mortality before hospital discharge) will be assessed using a logistic regression model adjusting for hospital and birth weight. The effect of the treatment on continuous secondary outcome (in-hospital growth) will be assessed using a regression model adjusting for hospital. Statistical analysis will be performed using R 3.2.2 software (R Foundation for Statistical Computing, Vienna, Austria) [11]. A *p* value less than 0.05 will be considered statistically significant.

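### The primary outcome is worded as a yes/no state per infant but modelled as a rate per reading, and the count that the model needs is never named

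*Protocol article*

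**What the plan says.** The Primary outcome measure section states: "The primary outcome measure will be whether the infants’ temperatures remain within the normal range", the range being 36.5–37.5 °C and the period that of KMC under the intervention. The abstract words it the same way. Readings are due "every 6 hours during KMC treatment", and the Procedure section sets the time frame: "The duration of the study will be until the patient’s discharge, with a maximum treatment duration of 7 days". After an abnormal reading the schedule changes: "In these cases, neonatal and maternal temperatures will be measured every hour until the normal range is reached".

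The Statistical analysis section gives the model: "The effect of the treatment on primary outcome will be assessed using a Poisson model adjusting for hospital and a set of clinically relevant confounders". It continues: "The logarithm of the number of measurements during hospital stay will be used as an offset, in order to take into account the different lengths". The same section uses the same Poisson-plus-offset form for the number of apnea episodes. It keeps logistic regression for sepsis and mortality, which it calls binary.

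**The concern.** In ordinary reading, whether temperatures remain in range is a yes/no state for each infant, and one abnormal reading ends it. A Poisson model with a log(measurements) offset describes something else: an expected count that grows in proportion to the number of readings. The article fixes both the outcome and the model, and they do not fit each other.

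Three things are at stake.

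- If the model is applied to the outcome as worded, length of stay enters the treatment ratio in a way that has nothing to do with temperature control.
- If a count was meant, the text does not say whether in-range or out-of-range readings are counted, and the two give very different ratios.
- The Data Safety and Monitoring Board section makes a significant primary-outcome difference in the first 100 infants one of the criteria for stopping for harm. The undefined variable therefore also feeds an interim decision.

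**Working it through.** The plan gives no figure to reproduce here: no in-range probability, effect size or power.

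**Inputs from the article.** Readings are 6-hourly, so 4 per day, and treatment lasts at most 7 days. The number of scheduled readings m therefore runs from 4 (one day) to 4 × 7 = 28. There are 150 infants per arm.

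**Assumptions, not in the article.** Each reading is in range with probability p between 0.90 and 0.98, readings are independent unless stated, and stay distributions are illustrative.

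**Step 1: what the offset imposes.** An offset of log(m) fixes E[Y] proportional to m. From m = 4 to m = 28 the expected outcome must rise by 28/4 = 7.

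**Step 2: how each candidate outcome behaves from m = 4 to m = 28.**

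| p | All in range, p^m | Ratio | Any out of range, 1 − p^m | Ratio | Count in range, mp | Ratio |
|---|---|---|---|---|---|---|
| 0.90 | 0.656 → 0.052 | 0.08 | 0.344 → 0.948 | 2.76 | 3.6 → 25.2 | 7 |
| 0.95 | 0.815 → 0.238 | 0.29 | 0.186 → 0.762 | 4.11 | 3.8 → 26.6 | 7 |
| 0.98 | 0.922 → 0.568 | 0.62 | 0.078 → 0.432 | 5.57 | 3.92 → 27.44 | 7 |

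Only the count matches the offset. With p = 0.95 and the coefficient of log(m) left free, simulated fits gave about −0.58 (all in range), 0.72 (any out of range) and 1.00 (count), against the imposed 1.

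**Step 3: effect on the treatment ratio, by hand.** Suppose the cap has no effect and every infant in an arm has the same number of readings, m1 (cap) or m0 (no cap). For the all-in-range outcome the offset model estimates

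(p^m1 / m1) ÷ (p^m0 / m0) = (m0/m1) × p^(m1 − m0), which should be 1.

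- 3 versus 4 days (12 versus 16 readings), p = 0.95: (16/12)/0.95^4 = 1.333/0.8145 = 1.64. At p = 0.90 it is 1.333/0.6561 = 2.03; at p = 0.98 it is 1.333/0.9224 = 1.45.
- 5 versus 4 days, p = 0.95: (16/20) × 0.8145 = 0.65.
- Half a day shorter (14 versus 16), p = 0.95: (16/14)/0.9025 = 1.27.
- Equal stay: exactly 1.
- Fully dependent readings within an infant: P(all in range) = p whatever m is, so 3 versus 4 days gives 16/12 = 1.33. Correlation shrinks the distortion but does not remove it.

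**Step 4: simulation with variable stay.** No cap effect, p = 0.95, 150 per arm, stay drawn as 1 plus a Poisson variable and capped at 7 days, 600 repetitions. The model had arm only, with robust standard errors. Entries are rate ratio and share with p < 0.05.

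| Mean stay, cap versus no cap | All in range | Any out of range | Count in range |
|---|---|---|---|
| 4 versus 4 days | 1.00, 3.7% | 1.00, 5.3% | 1.00, 5.2% |
| 3 versus 4 days | 1.57, 90% | 1.09, 15% | 1.00, 4.8% |
| 5 versus 4 days | 0.69, 70% | 0.94, 10% | 1.00, 6.3% |

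**Step 5: what stays open even with a count.** If 90% versus 95% of readings are in range, the ratio is 0.95/0.90 = 1.06 for in-range readings but 0.05/0.10 = 0.50 for out-of-range readings.

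The hourly repeats also matter. Take an infant with 28 scheduled readings, one of them abnormal, followed by three repeats of which two are abnormal. The in-range share is 27/28 = 0.96 on scheduled readings and 28/31 = 0.90 with repeats. It is 27/31 = 0.87 if repeats enter only the offset. The denominator now depends on the outcome.

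**The case against.** The strongest reply is that the Statistical analysis section shows what was meant. It sets logistic regression aside for outcomes that it calls binary, and gives the primary outcome the same form as the number of apnea episodes, which is a count. The outcome section never says that all readings must be in range. Read together, a count of readings per infant is the likelier intention, and for it the offset is right. This stands. It moves the fault to the outcome wording but does not remove it, because no section names the count. A full analysis plan might supply the coding, but it would then have to override the outcome as published.

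A reader might infer that the offset works in the wrong direction outright. The article does not support that. The sign is wrong only when the literal outcome is coded as success; coded as any reading out of range, the sign is right and only the size is off.

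A reader might also divide 7 by 0.0798 or by 0.292 and conclude that the trial result would be wrong by a factor of 88 or 24. Those quotients compare a one-day with a seven-day stay under assumed independent readings. They do not compare cap with no cap, and they do not measure bias in the treatment effect.

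Finally, nothing in the article shows that stay will differ between randomised arms. The one-day gaps used above are illustrations. The abstract does list age at discharge as a secondary outcome, so a difference is at least something the trial sets out to look for.

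**Conclusion.** The mismatch is real: the abstract and the Primary outcome measure section word a yes/no state, and the Statistical analysis section models a rate per reading whose numerator is not defined.

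How much it matters depends on the reading. Under a count, the model form is sound. What remains is an unnamed count and a denominator that hourly repeats can inflate after abnormal values. Under the literal all-in-range outcome, the treatment ratio is unbiased when stay is equal. It is distorted when stay differs: to about 1.6 or 0.7 for an assumed one-day difference in mean stay at p = 0.95, with no cap effect.

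Those sizes rest on assumed p, stay and independence. One result does not: adding readings can never raise the chance that all are in range, whereas the offset assumes a proportional rise.

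**What to change.** State one primary variable, in the same words, in the abstract, the Primary outcome measure section and the Statistical analysis section: the per-infant count of scheduled 6-hourly axillary readings within 36.5–37.5 °C, from randomisation to the earlier of discharge or day 7. A count of readings outside the range is equally workable, but one must be named. Define the offset as the log of the number of scheduled readings actually taken in that same window. Exclude the hourly repeats from both the count and the offset; they can still be recorded and reported.

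If the all-readings-in-range outcome is of interest, keep it as a secondary binary outcome, analysed without this offset.

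The cost is wording in three places, with no change to data collection beyond being able to tell scheduled from repeat readings. The registry entry was not available; if it carries the same wording, it should follow. The change should be made before any comparison by arm is seen, including the interim analysis of the first 100 infants.

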### Data Safety and Monitoring Board

Safety measures will include incidence, severity and causality of reported SAEs, represented by changes in occurrence of the expected common neonatal complications and the development of unexpected SAEs. SAE will be defined as unexpected death, apnea not responding to vigorous stimulation, severe hyperthermia (temperature >39 °C) and hypothermia (temperature <35 °C). All SAEs will be followed until complete resolution or until the clinician responsible for the care of the recruited patient considers the event to be chronic or the infant to be stable.

A monitoring board, including an independent assessor (not involved in the study) from the University of Padova and assessors from each participating hospital, will review all the deaths and adverse events. If there is a reasonable suspected causal relationship with the intervention, SAEs will be reported to the Ethics Committee to guarantee the safety of the participants.

An interim analysis will be performed on the primary endpoint and on SAEs from the first 100 enrolled infants. The interim analysis will be performed by the statistician, who is blinded for the treatment allocation and who will report to the PI. The PI will discuss the results of the interim analysis with the monitoring board and the trial will be ended in case of harm. Criteria for stopping for harm include: a statistically significant difference in the primary outcome between the treatment groups; and a reasonable suspected causal relationship between the intervention and SAEs.

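### The aim and primary outcome concern staying in the normal range, but no infant temperature is fixed at entry, so loss of normothermia cannot be told from never having had it

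*Protocol article*

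**What the plan says.** The Background section of the protocol article gives the aim as assessing the "effectiveness and safety of using a woolen cap in maintaining normothermia in low-birth-weight infants (LBWI) during KMC". The primary outcome is whether temperatures "remain within the normal range (36.5–37.5 °C) in the course of KMC during the intervention".

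The inclusion list is "Birth weight below 2500 g (and)Candidate to KMC treatment (and)Parental consent", and the exclusion list is "Major congenital malformationsTwinsParental refusal to participate in the study". Neither mentions temperature. The clinical gate is that infants are those "who are candidates for KMC, based on the clinical decision of the attending physician". The Procedure section refers to WHO guidelines for starting KMC but does not reproduce them. The Background describes a suitable infant as one where "the baby does not require special treatment, such as oxygen or intravenously administered fluids", again without mentioning temperature.

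Infant temperature is read every 6 hours during KMC (Primary outcome measure), at four fixed clock times (Guidelines for management). The Data collection section lists eligibility, antenatal history, randomization and the outcome data. The primary model in Statistical analysis adjusts for hospital, maternal temperature, environmental temperature, birth weight and postnatal age, with the log number of measurements as offset. Neonatal temperature appears only in the apnea model, without saying which reading is meant.

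The Data Safety and Monitoring Board section counts "severe hyperthermia (temperature >39 °C) and hypothermia (temperature <35 °C") among SAEs. It states no new-onset condition, but it does provide for causality assessment.

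**The concern.** To maintain a state, or to remain in it, one must first be in it. The article describes KMC as the best way of keeping a small baby warm, so a cold infant is a plausible KMC candidate, and nothing in the listed criteria keeps such an infant out. With no reading before allocation, the data cannot separate two questions: does the cap keep a warm infant warm, and does it help a cold infant recover? The mixture would be reported as maintenance.

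Three things are at stake:
- **Interpretation.** Out-of-range readings carried over from before allocation are counted alongside those that arise during KMC.
- **Sensitivity.** Carried-over readings occur in both arms regardless of the cap, and pull the estimate toward no effect.
- **Safety.** An extreme temperature present before the cap was applied can enter the SAE count, and so the interim review of the first 100 infants, with no reading to show that it came first.

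**Working it through.** **The plan's own figure.** The Sample size section gives 150 + 90 + 60 = 300, that is 150 per arm, which adds up. It rests on enrollment capacity, with no effect size or power, so there is no power figure to reproduce. Four readings a day for at most 7 days gives at most 4 × 7 = 28 scheduled readings.

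**Planned analysis (count per reading).** Assume out-of-range rates of 30% without and 20% with the cap, a true ratio of 0.20/0.30 = 0.667. Let a share f of infants in both arms carry k out-of-range readings over from entry, out of m readings. The observed rate in an arm with true rate r is

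[f·k + (m − f·k)·r] / m.

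Example with m = 8 (2 days), k = 2, f = 0.4: f·k = 0.8, so the rates are (0.8 + 7.2 × 0.30)/8 = 0.37 and (0.8 + 7.2 × 0.20)/8 = 0.28, and the ratio is 0.757.

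| Readings m | k | f = 0.1 | f = 0.2 | f = 0.4 |
|---|---|---|---|---|
| 28 (7 days) | 1 | 0.671 | 0.674 | 0.682 |
| 28 | 2 | 0.674 | 0.682 | 0.696 |
| 12 (3 days) | 1 | 0.676 | 0.684 | 0.701 |
| 12 | 2 | 0.684 | 0.701 | 0.731 |
| 8 (2 days) | 1 | 0.680 | 0.693 | 0.716 |
| 8 | 2 | 0.693 | 0.716 | 0.757 |

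The shift is small for long stays and grows only with short stays and a large f.

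One point could make it larger. The Procedure section calls for hourly readings after an abnormal temperature, and the offset is not limited to scheduled readings. If hourly readings count, an infant out of range at its first reading and back in range 6 hours later adds 5 extra readings. Over two days that gives 6 abnormal readings of 8 + 5 = 13, rather than 1 of 8. The article does not say which applies.

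**Infant-level reading (any out-of-range value is a failure).** This follows the wording of the outcome, but it is not the planned model. Assume failure rates of 50% versus 34% among infants in range at entry, and count the share f as failures in both arms. The observed rate is f + (1 − f)·p. Power with 150 per arm, two-sided 5%, is Φ{[d√n − 1.96√(2p̄(1 − p̄))] / √(p₁q₁ + p₂q₂)}:
- f = 0: 50% v 34%, power 80.5%
- f = 0.1: 55% v 40.6%, power 70.6%
- f = 0.2: 60% v 47.2%, power 60.5%
- f = 0.4: 70% v 60.4%, power 41.5%

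**Would analysing only infants in range recover the loss?** Assume 60% v 50% remain in range among those in range at entry, and 30% enter out of range (unpooled normal approximation).
- All 300 in range: z = 0.10/√((0.24 + 0.25)/150) = 1.75, power about 42%.
- Diluted, 0.7 × 60% = 42% v 0.7 × 50% = 35%: z = 0.07/√((0.42 × 0.58 + 0.35 × 0.65)/150) = 1.25, power about 24%.
- In-range infants only, 0.7 × 150 = 105 per arm: z = 0.10/√(0.49/105) = 1.46, power about 31%.

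Even here, restriction moves power from 24% to 31%, not to 42%.

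**Chance imbalance.** The 95% half-width of the between-arm difference in f is 1.96√(2f(1 − f)/n). With 150 per arm it is about 7, 9 and 11 percentage points at f = 0.1, 0.2 and 0.4. At the interim, taking 50 per arm and f = 0.2, it is 1.96 × √(0.32/50) = 0.157, about 16 points.

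**The case against.** Several stronger readings are tempting, and the article does not support them.

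- **Every abnormal entry temperature counts as a failure.** It does not. Only readings during KMC count, and the first may come up to 6 hours after the start. The abnormality must persist until then. Under the count model, one such reading does not make the whole infant a failure, and readings after recovery remain informative.
- **Febrile or severely hypothermic infants are admitted.** This is inferred from silence. The attending physician decides on candidacy, and the WHO starting rules are not shown. They may screen out some of these infants, or not.
- **The comparison is biased.** Allocation is 1:1 within hospital, so entry temperature is balanced in expectation. Enrolling all KMC candidates is also a legitimate pragmatic population.
- **Power falls from 42% to 24%.** That describes an infant-level pass/fail analysis under assumed rates, not the planned Poisson model.
- **SAE counts are corrupted.** Only the extreme thresholds are involved, causality is assessed, a board reviews the events, and SAE-based stopping requires a suspected causal link.

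It is also fair to say that a data sheet and a case report form exist and are not shown, so a starting temperature may be recorded there. That limits how much can be made of its absence from the data list. What remains is in the article itself: an aim and outcome worded for infants in range, criteria that do not require it, and a named covariate set that includes maternal and room temperature but not the infant's own starting value.

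**Conclusion.** The point holds in limited form. As the article describes it, the trial cannot separate infants who lost normothermia from infants who never had it, although maintenance is its stated aim. The cost is a blurred interpretation, some dilution toward no effect, and unmeasured chance imbalance, most noticeable at the interim look.

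Under the planned per-reading model the dilution is probably modest: a ratio of 0.667 becomes 0.67 to 0.76, with the upper end needing a two-day stay, two carried-over readings and 40% of infants out of range. It would be larger if hourly follow-up readings enter the count, or if the outcome were analysed as any value out of range. All rates and shares used here are assumptions. This is a worthwhile, inexpensive improvement, not a flaw that invalidates the randomized comparison.

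**What to change.** - Take one axillary reading with the study thermometer immediately before the envelope is opened, and record it.
- Leave eligibility and the full intention-to-treat primary analysis as they are. Add the starting temperature to the covariates of the primary model.
- Prespecify, as a supporting analysis, the primary outcome reported separately for infants in range and out of range at entry. The subgroups are defined before allocation, so randomization is preserved within them. The main conclusion should not move to the in-range group, which would give up precision.
- Flag temperature SAEs already present at entry and list them separately. Still count any new crossing of the threshold after return to range, because dropping every event in such infants would discard true recurrences.

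The cost is one extra reading per infant and a few lines of text. The in-range estimate rests on fewer infants and will be less precise. Enrollment began in January 2016, so infants already randomized may lack the reading unless it was recorded elsewhere. The first reading during KMC is not a substitute, because it comes after allocation.
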